#### Secondary outcomes

2.4.2

1.Intraoperative variables① Operating time: the time from the beginning of anal expansion to the end of the operation;② Intraoperative blood loss: taking a blooded soaked gauze as 5 mL;③ The weight and volume of the excised rectal mucosa removed by TST-33-MS and PPH.2.Postoperative complications① Anal pain

The visual analogue scale (VAS) method will be used, and 0 means no pain, 10 means the most pain. The VAS scores will be observed at 12 hours, 1, 2, 3, and 5 days postoperatively. Record the types and frequency of analgesics.

② Bleeding

Observe the bleeding at 12 hours, 1, 7, and 14 days after the operation. Mild bleeding: The bleeding can spontaneously cease; Moderate bleeding: The large bleeding should be stopped after conservative compression; Severe bleeding: The massive bleeding needs suture hemostasis operation when compression is ineffective.

③ Urinary retention

Observe and record the patients receiving at least one catheterization during hospitalization.

④ Anal edge edema

Observe the edema around the anal at 12 hours, 1, 7, and 14 days postoperatively. Grade I: no edema; Grade II: mild edema occupies less than one-fourth of the perianal region; Grade III: edema occupies more than one-fourth and half or more of the perianal area; Grade IV: edema occupies more than half of the perianal area.

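### Anal edge edema Grades III and IV overlap for every extent above one-half, so the same patient can be graded either way

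*Protocol article*

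**What the plan says.** Anal edge edema is the last of the postoperative complications listed in section 2.4.2 (Secondary outcomes) of the protocol article. The schedule is "Observe the edema around the anal at 12 hours, 1, 7, and 14 days postoperatively", and Table 1 shows the same four times. The scale has four grades, ordered by extent. The lowest means that edema is absent, and the second covers mild edema with an upper limit just short of one-fourth. The highest is printed as "Grade IV: edema occupies more than half of the perianal area". The one directly beneath it, the third, is defined by the phrase "edema occupies more than one-fourth and half or more of the perianal area", which sets no upper limit.

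The article contains no other definition of these grades. Table 1 gives assessment times only, and section 2.5 (Statistical methods) does not mention the scale. No rule says which grade applies when two definitions are met.

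**The concern.** An ordered scale has to give each observation one grade and only one. Here the two highest grades are both open at the top, so severe edema fits either.

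What is at stake is the line between III and IV. It decides any count of the worst grade. It also decides the value that enters a rank comparison, such as the Mann–Whitney test that section 2.5 names for non-normal data. Two assessors could give different grades to the same patient at the same visit, and both would be following the protocol. That adds noise to a named secondary outcome and makes published grade frequencies hard to interpret.

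**Working it through.** There is no stated figure to reproduce. The check is interval logic on the four definitions.

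**Inputs** (all from section 2.4.2). Let x be the fraction of the perianal area with edema, from 0 to 1.

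- Grade I: x = 0
- Grade II: 0 < x < 1/4
- Grade III: depends on how the printed phrase is read (see below)
- Grade IV: x > 1/2

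**Readings of Grade III**

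- *Span*: x > 1/4, with extents of one-half and above included. This follows the printed words.
- *Conjunctive*: x > 1/4 and x ≥ 1/2, both required. This also follows the printed words, but the first condition then does no work.
- *Probable intention*: 1/4 < x ≤ 1/2. This needs the printed direction at one-half to be reversed.

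**Method.** Every extent from 0% to 100% in steps of 1% was assigned to each grade whose wording it meets.

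| Reading of Grade III | Extents meeting both III and IV | Extents meeting no grade |
|---|---|---|
| Span | 51% to 100% (50 values) | 25% only |
| Conjunctive | 51% to 100% (50 values) | 25% to 49% (25 values) |
| Probable intention | none | 25% only |

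**Worked cases**

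- x = 0.60: 0.60 > 1/4 and 0.60 ≥ 1/2, so it is Grade III on either printed reading. Also 0.60 > 1/2, so it is Grade IV. It has two grades.
- x = 0.50: Grade III on all three readings. It is not Grade IV, because 0.50 is not above 1/2. It has one grade.
- x = 0.40: Grade III on the span reading and on the probable intention. It has no grade on the conjunctive reading.
- x = 0.25: not below 1/4, so not Grade II; not above 1/4, so not Grade III. It has no grade on any reading.

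**Result.** On both readings that respect the printed words, the overlap covers all of Grade IV and is not confined to a boundary point. Only the reading that reverses the printed direction removes it, and that reading still leaves exactly one-fourth ungraded.

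**Exposure.** With the 204 patients planned in section 2.2.1 and four assessments each, there are at most 204 × 4 = 816 gradings. The article gives no expected distribution of edema, so the number above one-half cannot be derived.

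**The case against.** The best defence is that this is a language slip and the intention can be recovered. The grades rise with extent, and Grade IV's own lower limit implies that Grade III should stop at one-half. An assessor used to ordered scales would probably give edema above one-half the higher grade. The article is also a condensed account, and the working form may already carry clean cut-points. All of this is fair, and it is why the point is minor. It does not remove the point: the article leaves no grade out, but prints all four, and two of them conflict.

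A reader might infer three stronger things that the document does not support.

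- *That unmasked assessors could use the overlap to favour one arm.* The abstract and section 2.1 both describe the trial as evaluator-blinded. Section 2.2.4 names only surgeons and patients as unblinded. If evaluators are masked as stated, confusion between III and IV should be largely non-differential, adding noise and not a systematic advantage.
- *That the overlap falls where the arms are most likely to differ.* No section predicts a contrast in severe edema. The Introduction credits the combined procedure used in the control arm with less postoperative edema, which gives no ground for expecting the arms to separate at Grade IV.
- *That everything from one-fourth upward cannot be graded.* This follows only from the conjunctive reading, the least plausible one, because it makes the one-fourth condition redundant.

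The gap at exactly one-fourth is also slight. Nothing suggests that extent is measured finely enough for a single boundary value to matter.

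**Conclusion.** The point holds as a self-contradiction in a stated outcome definition. Grades III and IV both cover every extent above one-half, and the text offers no way to choose between them. Exactly one-fourth falls in no grade, which is a minor companion defect.

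The size is small. The likely effect is misclassification between two adjacent grades of one secondary outcome at up to four visits per patient. The primary outcomes (anal function and recurrence) do not use this scale, and the sample size rests on recurrence.

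The conclusion assumes only that the grades are applied as printed. If the working form already has a clear upper limit for Grade III, the error is confined to the article and needs correcting there. No claim of bias towards either arm is made.

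**What to change.** Replace the four definitions in section 2.4.2 with grades that do not overlap and leave no gap:

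- Grade I: no edema (x = 0)
- Grade II: above 0 and below one-fourth
- Grade III: one-fourth to one-half, both limits included
- Grade IV: above one-half

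Every extent from 0 to 1 then meets exactly one grade: 0.25 and 0.50 go to III, and 0.60 goes to IV only. Use identical wording on the case report form. If the form already has different cut-points, bring the article and the form into agreement and state which were applied.

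The cost is one sentence in section 2.4.2 and the matching line on the form. Sample size, visit schedule and analysis methods do not change.

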#### Safety evaluation

2.4.3

All possible adverse events (AEs) will be recorded on the Serious Adverse Event Report form, such as bleeding, anal stenosis, anal fissure, pain, urinary retention, anal fistula, prolapse, difficulty in defecation, urgency of stool, pelvic sepsis, systemic complications, and itching. In addition, AEs forms will record all deaths due to any cause during the course of the study.

### Statistical methods

2.5

Statistical analyses will be performed using the Statistical Package for the Social Sciences (SPSS) v22.0 software (SPSS Inc., Chicago, IL). Statistical testing is 2-sided and *P* < .05 is considered statistically significant. Efficacy outcomes are analyzed on an intent to-treat (ITT) basis who has at least 1 follow-up, and the last observation carried forward rule will be applied to manage missing data. Considering the homogeneity, group T test for normally distributed data or Mann–Whitney *U* test for non-normally distributed data will be used to compare variables between groups. For differences within each group, repeated measured analysis of variance will be used for assessments in different time points, whereas Wilcoxon signed-rank test will be selected for non-normally distributed data.

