#### Participants and sample size

2.2.1

Participants meet the inclusion and exclusion criteria in this RCT will be mainly recruited from inpatients of proctology department in Changshu Hospital of Traditional Chinese Medicine.

According to the previous report, the recurrence rate of PPH in the treatment of hemorrhoids was 9.6%. According to the preliminary experiment, the recurrence rate of severe prolapsed hemorrhoids by the TST-MS combined with anal canal epithelial preservation operation was 0%. Taking α = 0.05 and β = 0.2, 85 samples will be needed in each group. Considering the withdrawal rate of 20%, the total number of patients is determined as 204, that is 102 in each group.

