### Outcome variables

2.4

Follow-up of visits to the hospital is required at week 2 and 4 after surgery, and telephone follow-ups are conducted at week 3, 8, and 1 year after the operation, to report and record the following variables (Table 1).

**Table 1 T1:** Outcome variables assessed during the study.

			Post-operation							Follow up			
				
	Preoperation	Intraoperation	12 h	Day 1	Day 2	Day 3	Day 5	Day 7	Wk 2	Wk 3	Wk 4	Wk 8	1 y
Primary outcomes													
Anal function													
Incontinence score	✓										✓		
Circumference of anal canal	✓										✓		
Recurrence										✓	✓	✓	✓
Secondary outcomes													
Operating time		✓											
Intraoperative blood loss		✓											
Weight and volume of excised specimen		✓											
Anal pain			✓	✓	✓	✓	✓						
Bleeding			✓	✓				✓	✓				
Urinary retention			✓	✓	✓	✓	✓	✓	✓				
Anal edge edema			✓	✓				✓	✓				

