#### Primary outcomes

2.4.1

1.Anal function① Incontinence score:Wexner score will be used to evaluate the anal function of patients before and 4 weeks after the operation.② Circumference of the anal canalMeasure the circumference of the anal canal once before and 4 weeks after the operation.2.Recurrence of internal hemorrhoids and residual external hemorrhoids

Re-prolapse and obvious bleeding of internal hemorrhoids after the operation can be regarded as recurrence. Count the number of recurrences and residual recurrences of external hemorrhoids within 1 year after the operation.

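### Last observation carried forward counts unobserved months as recurrence-free and turns a missing week-4 function value into no change since before surgery

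*Protocol article*

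**What the plan says.** Section 2.5 (Statistical methods) fixes the missing-data rule: "the last observation carried forward rule will be applied to manage missing data". It makes no exception for any outcome and names no alternative analysis. The same section defines who is analysed: "Efficacy outcomes are analyzed on an intent to-treat (ITT) basis who has at least 1 follow-up".

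The primary outcomes in section 2.4.1 are recurrence and anal function.

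- **Recurrence:** "Count the number of recurrences and residual recurrences of external hemorrhoids within 1 year after the operation". Table 1 places its assessment at weeks 3, 4, 8 and 1 year. Week 4 is a hospital visit; for the rest, "telephone follow-ups are conducted at week 3, 8, and 1 year after the operation".
- **Anal function:** "Wexner score will be used to evaluate the anal function of patients before and 4 weeks after the operation". Anal canal circumference has the same two time points.

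Section 2.2.1 plans on recurrence of 9.6% in the control arm and 0% in the new arm, and raises 85 per group to 102 for 20% withdrawal.

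**The concern.** Carrying a value forward is defensible only if the outcome would have stayed where it was last seen. Neither type of primary outcome fits that.

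Recurrence accumulates. A patient without recurrence at week 8 is still at risk for the rest of the year, and the rule records that unobserved time as free of recurrence. The error can only lower the absolute rate.

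For Wexner score and circumference there is no postoperative value before week 4. The only value available to carry is the preoperative one, so the analysis would use a measurement taken before the operation as the result of the operation. That hides harm and benefit alike. If carrying a preoperative value was not intended, the rule has nothing to carry for these two outcomes and cannot be applied. The text does not say which is meant.

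At stake are the 1-year recurrence rates, the comparison between arms if loss differs, and the size of any functional change.

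**Working it through.** **Inputs from the protocol article**

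- Control recurrence p = 9.6%, new operation 0%, withdrawal 20%, 102 per arm (section 2.2.1).
- Recurrence contacts at weeks 3, 4, 8 and 1 year; function before surgery and at week 4 (section 2.4, Table 1).

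**Assumptions, not in the protocol**

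- L, the share of recurrences that occur after week 8: 50%, 80% or 100%.
- d, the share of an arm lost between the week-8 and 1-year contacts: 20% in both arms, or 10% versus 30%.
- Loss is unrelated to recurrence.

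**The plan's own figure.** The protocol states: "Taking α = 0.05 and β = 0.2, 85 samples will be needed in each group". For 9.6% versus 0%, two-sided, the usual formulas give 77 (pooled), 74 (unpooled) and 97 (pooled with continuity correction). Fisher's exact test first reaches 80% power at 81. None gives 85. The step to 102 is 85 × 1.2. Nothing below depends on the 85.

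**Unobserved time.** 52 − 8 = 44 weeks for a patient last reached at week 8, and more for one lost earlier.

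**Scale.** 102 × 0.20 = 20.4 patients per arm could have a carried-forward status (17 by the plan's own 102 − 85). Expected control recurrences are 102 × 0.096 = 9.8. Carried-forward non-events could outnumber real events.

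**Recurrence.** Recorded rate = p × (1 − d × L). For example, 0.096 × (1 − 0.2 × 0.5) = 0.0864.

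| L | 20% lost | 10% lost | 30% lost | Gap, 10% v 30% |
|---|---|---|---|---|
| 50% | 8.6% | 9.1% | 8.2% | 1.0 point |
| 80% | 8.1% | 8.8% | 7.3% | 1.5 points |
| 100% | 7.7% | 8.6% | 6.7% | 1.9 points |

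The last column assumes the same true 9.6% in both arms, so the whole gap is produced by the rule. With 20% lost in both arms the gap is zero. If some patients are lost before week 8, early events are missed too, and the recorded rate moves towards 0.096 × 0.8 = 7.7%.

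**Power** (Fisher, 102 per arm, 9.6% versus 0%): 93% with complete data. With 20% lost and carried forward it is 88% at L = 50% and 80% at L = 100%. Analysing only about 82 completers per arm gives about 81%.

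**Function.** With share m missing at week 4 and set to the preoperative value, recorded mean change = (1 − m) × true mean change. This gives 95%, 90% and 80% of the true change at m = 5%, 10% and 20%. The 20% is an upper bound, because the protocol gives it for the whole trial and not for week 4. The formula assumes missingness unrelated to outcome.

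**Check of the alternative for recurrence.** Take L = 80% and 20% lost after week 8. A grouped life table has risk 0.096 × 0.2 = 0.0192 up to week 8. The risk afterwards, among those still observed, is 0.0768 / 0.9808 = 0.0783. Cumulative risk = 1 − 0.9808 × (1 − 0.0783) = 0.096, so the true rate is recovered under the stated assumption about loss.

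**The case against.** The strongest case on the other side is that the effect is small and mostly works against the new operation.

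- **Size.** With 20% lost in both arms, the control count falls by about 1 to 2 patients of 102 (102 × 0.0096 = 1.0; 102 × 0.0192 = 2.0). This stands. The main harm is bias in the rates, since power is no worse than in a completers-only analysis.
- **Direction.** A reader might infer that the rule manufactures a benefit. At the planning rates and with equal loss it lowers only the control rate and so dilutes the difference. A false difference needs unequal loss. The protocol does not predict that, although unblinded patients and surgeons (section 2.2.4) make it possible.
- **Who is affected.** A reader might infer that everyone lost after week 8 becomes a non-event. A recurrence already recorded stays counted. Residual external hemorrhoids, counted within the same outcome, can be recorded from week 3, so late loss matters less for them.
- **Function.** Week 4 is a required visit, so missingness may be well below 20%. Stenosis and difficulty in defecation are also recorded as adverse events (section 2.4.3), so narrowing is not seen only through circumference. Both points stand, but neither makes a preoperative value a valid week-4 result.
- **Analysis set.** A reader of Table 1, where the follow-up heading begins at week 3, might infer that everyone lost before then is dropped. The text of section 2.4 treats week 2 as a follow-up visit, so that reading is not supported. A patient seen only at week 2 is in the set, with no recurrence assessment to carry forward.
- **Alternatives.** Censoring at week 8 also rests on an assumption that cannot be tested. This stands and is why a sensitivity analysis is needed.

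**Conclusion.** The point holds. The rule is stated in the text and, followed as written, affects every primary outcome.

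- Absolute 1-year recurrence is understated: a true 9.6% reads as 8.6% to 7.7% with 20% loss in both arms and 50% to 100% of recurrences after week 8.
- With unequal loss the arm that loses more patients is favoured: 8.8% versus 7.3% under assumed losses of 10% and 30%, 80% of events late and equal true rates.
- Mean functional change shrinks by the share missing at week 4, with 20% as the upper bound.

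The timing of recurrence and the split of losses are assumptions, since the protocol gives neither. A reader might also infer that standard errors come out too small because carried values are treated as observed. That has not been calculated here and is not part of the conclusion.

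**What to change.** Delete last observation carried forward for the primary outcomes and replace it as follows.

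- **Recurrence.** Estimate 1-year cumulative recurrence per arm by a grouped life table over the scheduled contacts, censored at last contact. Report the difference with a confidence interval. Add a sensitivity analysis that varies the unknown 1-year status, for example worst case or tipping point. The grouped form suits the data: the protocol asks for a count and does not mention recurrence dates, so a finer time-to-event analysis would need dates to be collected.
- **Wexner score and circumference.** Compare week-4 values adjusted for the preoperative value, with multiple imputation for missing week-4 values. Never use the preoperative value as the outcome.
- **Analysis set.** Keep all randomised patients in their allocated group, or call the set that requires one follow-up modified ITT.

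The cost is a change of wording and a little more analysis work. The reported recurrence rate may be slightly higher. The visit schedule does not change.

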## Discussion

3

The single PPH technology for all prolapsed hemorrhoids is no longer in line with current clinical needs, which makes it an important issue to improve the surgical instruments and operation methods, as far as possible to solve the contradiction between curative effect and complications, and to expand the indications. It has become an important problem to be solved in the operation of severe prolapsed hemorrhoids. Therefore, to improve the clinical efficacy reduce the recurrence rate, and protect the anal function for severe prolapsed hemorrhoids, we try to improve PPH technique and expand the indications of stapler to completely preserve the anal cushion and epithelium. Compared with the conventional MMH technique, our novel operation could reduce the damage to the tissues, which will make it faster to heal and cause fewer complications, and compared with current PPH operation, it can significantly reduce postoperatively prolapsed internal hemorrhoids and residual external hemorrhoids, and expand the indications of the stapler, so as to cure hemorrhoids while protecting the anal function.

However, there are still some limitations in this protocol. First, due to the different operation methods, this study cannot be double-blinded, which may lead to certain biases. Second, this study is a single-center study, and the source of patients is relatively single and limited, which may affect the conclusions to a certain extent.
